### Participants

#### Patients

A total of 120 patients will be recruited at the Center of Mental Health and
Psychotherapy (CMHP), an outpatient training and research center for CBT at
Witten/Herdecke University, Germany. General inclusion criteria will be as
follows: (1) psychotherapy outpatient, (2) at least one mental disorder
according to DSM-5 criteria, (3) at least 18 years of age. General exclusion
criteria will be as follows: (1) current diagnosis of a severe episode of
major depressive disorder, (2) suffering from a psychotic disorder, (3)
suffering from substance use disorder, (4) current episode of (hypo)mania,
(5) current suicidal risk, (6) extensive experiences with guided mental
imagery interventions (two or more interventions in prior treatment
settings), (7) insufficient German language skills, (8) currently receiving
another psychological treatment. Prescribed medications for anxiety or
depressive disorders do not lead to exclusion from the study. The presence
of comorbidities does not result in exclusion from the study.

**Figure 1 f1:**
[figure not shown]
Flowchart of Study Design *Note*. a = session questionnaires: Positive and
Negative Affect Schedule (PANAS), Single-item mood scaling,
Multiperspective Assessment of Change Mechanisms in Psychotherapy
(SACiP-RA), Working Alliance Inventory – Short Revised (WAI-SR),
Short version of Derogatis Symptom Checklist (SCL-K-9); BSI = Brief
Symptom Inventory; CD-RISC = Connor-Davidson Resilience Scale; CMHP
= Center of Mental Health and Psychotherapy; GSE = General
Self-Efficacy Scale; RSES = Rosenberg Self-Esteem Scale; SCID =
Structured Clinical Interview according to DSM-5 criteria; SUIS =
Spontaneous Use of Imagery Scale; WAI-SR = Working Alliance
Inventory – Short Revised; WIRF = Witten Strengths and Resource
Form.

A power analysis with G*Power (Faul et al., 2007) based on effect sizes from relevant studies (Flückiger et al., 2016; Willutzki et al., 2004) was conducted
to determine sample size. The detection of a small to moderate effect
(Cohen’s *f* = 0.15) for the interaction between time (pre,
mid-4, mid-8, post-12) and treatment condition (PMI vs. NMI vs. TAU) [mixed
model analysis of variance (ANOVA), within-between-interaction, α = .05,
power = .80, number of groups = 3, number of measurements = 4, pre-post
correlation = .50, non-sphericity correction = 1] resulted in a sample size
of 78 patients. Considering possible dropouts, we will recruit up to 120
patients. Power analysis of a repeated measurement ANOVA is comparable to
multilevel models (MLM; Baldwin et al., 2014).

#### Therapists

20-25 therapists will be recruited at the CMHP. All therapists have at least
a master’s degree in psychology. Both, licensed CBT therapists and
therapists in advanced CBT training will take part in the study. Trainee
therapists have at least one year of clinical experience before they start
treatments in the CMHP. Parallel to the study, trainee therapists take part
in 600 hours of practice-based workshops as a part of CBT training protocols
in Germany. Therapists participate in 90-minute supervision in small groups
on a weekly basis (general clinical supervision, not study-specific). Every
therapist in the CMHP will be informed about study procedures in small group
meetings of approx. 30 minutes conducted by [name].

### Standard Procedure at CMHP

Adult patients with various types of mental disorders receive treatment by
approximately 20 licensed CBT therapists resp. trainee therapists. The CMHP has
eight rooms for providing psychotherapy. All rooms are fully equipped with video
and audio recording. Computer-assisted psychometric assessments during therapy
are standard procedures at the CMHP and regularly reviewed by staff members.
Personal and treatment-specific data is managed with a software called AmbOS. To
promote data quality, fixed schedules of assessments for patients and therapists
were included. Patients interested in a CBT treatment have a first phone contact
and a one-session consultation with a licensed therapist. They are then listed
on an internal waiting list (with currently on average six months waiting time).
Patients are contacted by a therapist and invited to a standardized diagnostic
phase. The diagnostic phase includes four to five sessions with the following
order: exploration and treatment consent, Structured Clinical Interview for
DSM-5 Disorders (SCID; Beesdo-Baum et al., 2019), biographic work, situation analysis. After the diagnostic
phase, a CBT treatment according to the German health system is offered.

### Development of the Micro-Interventions

A systematic literature search of interventions to foster PA was conducted,
indicating positive mental imagery as a promising strategy. Important aspects to
boost emotional experiences in imagery interventions were identified based on
relevant studies (e.g. Grol et al., 2017;
Holmes et al., 2008). Procedures of
positive and neutral interventions used in these studies are screened in detail.
Based on this information, we developed a first version of the PMI in a
six-minute format. Next, eleven therapists piloted-tested the intervention with
25 different patients regarding its practical implication. Therapists conducted
the intervention within treatment sessions. An anonymous survey was conducted,
in which patients and therapists described positive and critical aspects of the
intervention independently. We reformulated the intervention script, based on
this feasibility information, to its final version. The NMI script was
parallelized. Scripts for both interventions can be found in the Appendix (see
Supplementary Materials).
We decided to record the interventions on audiotapes that will be played at the
start of each treatment session to increase standardization (inspired by the
PrOMET-study by Mander et al., 2019).
Both interventions are spoken and recorded by UW. The audiotapes will be played
on bluetooth speakers (Anker SoundCore Mini). Two loudspeakers (grey: PMI;
black: NMI) are installed in every therapy room.

### Conditions and Experimental Session

All three conditions will be parallelized and include a CBT treatment based on an
individual case conception. Every session will start with an initial greeting of
patients and the start of video recording.

Experimental sessions will be conducted from session one to eight in the active
conditions. In each experimental session of the PMI condition, a grey
loudspeaker will be placed on a table in front of patient and therapist with on
average one-meter distance. The therapist will carry out the mood scaling by
asking the patient to rate his/her mood in the present moment from one (very bad
mood) to ten (very good mood). After that, therapists will start the record of
the PMI (duration about six minutes). Patients are guided to imagine a positive
situation from the last week. Directly after the micro-intervention, the same
mood scaling will be conducted again. At the end of the intervention, patients
are instructed to communicate the content of their imagination with their
therapist for about one minute. After completion, the regular CBT session will
begin. After each session patients will complete session questionnaires.
Procedures of the experimental sessions in the NMI condition will be
parallelized to the description above. At session start, the micro-intervention
will be performed with a black speaker with the instruction to imagine a
non-emotional situation within the last week. In the control condition, standard
CBT will be conducted without additional micro-intervention.

### Study Course From Patients’ Perspective

Figure 2 shows the study course from
patients’ perspective. Patients will get a short-information about the studies
objectives and procedures within in the first session of the diagnostic phase.
If interested, a study coworker will contact them for an additional meeting.
Patients will receive written and verbal study information in this meeting and
will sign informed consent. It will be emphasized that study participation is
voluntary with the option to revoke study participation at any time without
reasons and/or disadvantages. Patients in both active conditions will receive an
introduction to the respective mental imagery intervention, including
cooperative exploration of specific contents (situation imagery as detailed as
possible, sensory modalities, field perspective), examples of positive/neutral
situation in the their life, and a practice of the respective intervention.
Furthermore, possible difficulties with the interventions will be discussed. The
study coworkers will educate patients how to handle it if they fall out of their
imagination during the intervention. After the diagnostic phase, all patients
will run through twelve CBT sessions. Patients will receive session
questionnaires directly after each session. Additional measurements after every
forth session will be included in the study.

**Figure 2 f2:**
[figure not shown]
Study Course From Patients’ Perspective

### Measures

Table 1 provides an overview of all
measures and their application in the study.

**Table 1 t1:** Application Plan of Measures

Measures	Pre	Session by Session	Measurement waves		
			Mid-4	Mid-8	Post-12
Session questionnaires					
Mood scaling		1-12			
Positive and Negative Affect Schedule (PANAS)	x	1-12			
Resource activation (SACiP-RA)	x	1-12			
Working-Alliance-Inventory (WAI-SR)	x	1-12			
Short version of Symptom-Checklist (SCL-9-K)	x	1-12			
Clinical assessment					
Witten Strengths and Resource Form (WIRF)	x		x	x	x
Connor-Davidson Resilience Scale (CD-RISC)	x		x	x	x
Rosenberg Self-Esteem Scale (RSES)	x		x	x	x
Brief Symptom Inventory (BSI)	x		x	x	x
General Self-Efficacy Scale (GSE)	x				
Spontaneous Use of Imagery Scale (SUIS)	x				
Observer Rating					
Resource-oriented micro-process analysis (ROMA)		2nd, 5th, 8th session			

*Note*. pre = baseline scores; mid-4 = assessment after
fourth sessions; mid-8 = assessment after eighth session; post-12 =
final assessment after twelfth session.

#### Process Analysis – Primary Outcome

##### Session Questionnaire I

To assess PA and NA of patients, we will apply the Positive and Negative
Affect Schedule (PANAS; Krohne et al., 1996). The PANAS is an internationally used 20 item
self-report. As described, affect is defined as the subjective
experience of an emotional state and is mostly differentiated by
positive versus negative valence (Hofmann, 2016). Participants will be asked to rate the items
according to how they feel "in the current moment". Two subscales of
global PA (ten items, range: 1-5) and global NA (10 items, range: 1-5)
will be used. Item examples are shown in the following: “Indicate the
extent you feel this way in the current moment - Proud (global PA); -
Nervous (global NA). Both scales have shown good internal consistency
(PA: α = .85, NA: α = .86) and are widely validated (Krohne et al., 1996).

#### Process Analysis – Further Measures

##### Session Questionnaire II

Mood scaling – a single-item mood scaling (“How do you feel in the
present moment?”) will be used as an economical assessment of affect.
Patients will be asked to rate their mood on a scale from one (very bad
mood) to ten (very good mood). Various short measures of mood were
applied in previous studies: These instruments showed practicability and
content validity (high correlation with measures of depressive mood) in
clinical samples, especially for visual mood scales (Ahearn, 1997; Luria, 1975). Moreover, Van Rijsbergen et al. (2014) showed the
transferability of these results for a verbal single-item mood rating.
The mood scaling will be used: (1) as a session questionnaire directly
after each of the twelve sessions; (2) as an evaluation instrument of
the mental imagery micro-interventions in the active conditions (mood
scaling before and after the micro-intervention, see conditions and
experimental sessions). We decided to include a further affect measure,
additionally to the PANAS, because of the simple use of the single item
mood scaling in therapy sessions. It is also included as a session
questionnaire to analyze the post-hoc correlation between the mood
scaling and the PANAS to check construct validity of the single-item
measure.

##### Session Questionnaire III

To assess levels of resource activation from patients’ perspective, we
will apply the subscale resource activation of the Scale for the
Multiperspective Assessment of Change Mechanisms in Psychotherapy
(SACiP-RA; Mander et al., 2013).
Resource activation refers to transdiagnostic change processes in
therapy where strengths or potentials of the patient become perceptible
and are used in treatment sessions (Grawe & Grawe-Gerber, 1999). The instrument was included
based on prior findings, indicating the association of PA and in-session
resource activation (e.g. Flückiger et al., 2009). The subscale consists of three items (range:
0-4). Items of the SACiP-RA were developed based on the Bern Post
Session Questionnaire, an established therapy process measure (Flückiger et al., 2010). Item
example: “In today’s session, I felt where my strengths lie.” The
subscale has displayed good internal consistency (α = .71) and
significant associations with treatment outcome (Mander et al., 2013).

##### Session Questionnaire IV

To assess quality of the therapeutic alliance, we will apply the Working
Alliance Inventory – Short Revised (WAI-SR; Wilmers et al., 2008). We decided to include the
WAI-SR as a process measure to analyze its association with PA within
and between sessions. Based on prior studies, we expect that patients
report better alliance directly after sessions with high levels of PA
(Chui et al., 2016).
Furthermore, we want to analyze whether PA and the working alliance will
develop parallel in the process of treatment. The WAI-SR is an
internationally used 12 items self-report of therapeutic alliance
measuring bond, goals and tasks in psychotherapy based on feedback of
patients concerning the current therapy session. Items are answered on a
likert scale from one to five. Item example: “My therapist and I respect
each other.” The WAI-SR is considered the gold standard in alliance
assessment with excellent psychometric properties and outcome prediction
(Horvath et al., 2011).

##### Session Questionnaire V

To assess general psychopathology, we will apply the short version of
Derogatis Symptom Checklist (SCL-K-9; Klaghofer & Brähler, 2001). We decided to include the
SCL-K-9 as a process measure to analyze its association with PA within
and between sessions (e.g. parallel development of increase of PA and
improvement in symptoms). The short version with nine items (range: 0-4)
is an internationally used self-report. Item example: “During the last
past seven days, how much were you distressed by: finding it difficult
to start something.” The short version has shown good internal
consistency (α = .87) as well as high correlations to the original
version (Petrowski et al., 2019).

#### Intervention Analysis – Primary Outcome

##### Subjective Resources of Patients

Witten Strengths and Resource Form (WIRF; Victor et al., 2019). As described, psychosocial resources
were defined as positive and functional aspects of a person or his/her
environment (Taylor & Broffman, 2011). The instrument assesses a generic perception of
resources rather than separate positive aspects. Therefore, it measures
the internal evaluation of a person’s inherent resources. This
subjective perception should be differentiated to the therapeutic
process of resource activation. The WIRF is a self-report with 37 items
(range 0-5). In our study we will use a total score of resources in the
context of current problems (12 items). Item example: “I am dealing with
my current difficulties and problems by – actively tackling tasks.” The
scale has displayed good internal consistency (α = .88), evidence for
convergent and divergent validity as well as evidence of change
sensitivity in the course of psychotherapy (Schürmann-Vengels et al., 2022; Victor et al., 2019).

##### Resilience of Patients

Connor-Davidson Resilience Scale (CD-RISC; 10 Item version, German
adaption by Sarubin et al., 2015). As described, psychological resilience is a dynamic and
multidimensional trait that enables a successful adaptation to
adversities and stressors (Connor & Davidson, 2003). The CD-RISC is an internationally used
self-report (range 1-7) to access general resilience. Item example: “I
am able to adapt when some things change”. The German adaptation with 10
items has shown good internal consistency (α = .84), good
retest-reliability (*rtt* = .81, *p* <
.001) and evidence for convergent validity (Sarubin et al., 2015).

##### General Self-Esteem

Rosenberg Self-Esteem Scale (RSES; von Collani & Herzberg, 2003). As described, self-esteem is
defined as the degree, a person positively consider his/her
characteristics or abilities (Brown, 2007). The RSES is an internationally used self-report with
10 items (range 0-3) to assess a sum score of general self-esteem. Item
example: “I am able to do things as well as most other people.” The
German version shows good internal consistency (α = .83-.88) as well as
evidence of criterion and construct validity (von Collani & Herzberg, 2003).

#### Intervention Analysis – Secondary Outcome

##### General Psychopathology

Brief Symptom Inventory (BSI; Franke, 2000). The BSI is an internationally used self-report with 53
items (range 0-4). The BSI was chosen as an outcome measure of the
intervention analysis to analyze the effects between conditions on
symptom improvement. We decided to include this version in addition to
the economical process measure of psychopathology (SCL-K-9), because its
subscales delivers specific information on the improvement of different
mental disorders and it is more comparable to outcome measures in other
intervention studies. Item example: “During the last past seven days,
how much were you distressed by: feeling lonely.” The German version has
shown excellent psychometric properties in clinical samples and is one
of the most used instruments in psychotherapy research (Geisheim et al., 2002).

##### Working Alliance

WAI-SR (Wilmers et al., 2008).
Description of the instrument, see process analysis – further measures.
We further included the WAI-SR as a secondary outcome to analyze whether
the conditions have specific influence on general alliance.

#### Further Measures

##### Self-Efficacy

General Self-Efficacy Scale (GES; Schwarzer & Jerusalem, 1999). Self-efficacy refers to
the subjective belief that a person is confident that his/her actions
lead to successful/targeted outcomes (Bandura, 1977). Several studies have suggested the
beneficial effects of self-efficacy on mental health (e.g. Schönfeld et al., 2016). The GES
was, therefore, included as a possible predictor of the slope of PA and
NA in the process analysis. The GES is an internationally used
self-report with ten items (range 0-3). Item example: “I can always
manage to solve difficult problems if I try hard enough.” The instrument
has shown excellent internal consistency (α = .80-.90) as well as good
predictive quality in psychotherapeutic contexts (Schwarzer & Jerusalem, 1999).

##### General Mental Imagery Ability

Spontaneous Use of Imagery Scale (SUIS; German adaptation by Görgen et al., 2016). The SUIS is
an internationally used self-report. The German adaptation consists of
17 items (range 1-5) and showed good internal consistency (α = .85),
evidence for convergent validity as well as high correlations to the
original scale (Görgen et al., 2016). Item example: “When I think about visiting a relative,
I almost always have a clear mental picture of him/her.”

#### Observer Rating

To assess relevant aspects on a minute-by-minute basis within treatment
sessions, the Resource-oriented Microprocess Analysis will be applied (ROMA;
Flückiger & Grosse Holtforth, 2008). The instrument is a coding system of different aspects of
resource activation (personal resources, motivational resources, reframing
of problems, global resource activation) and PA from video recordings of
treatment sessions. The coding system has shown good to excellent interrater
reliability for patients and therapists (Κ = .82 - .99).

Independent research assistants will analyze the videotapes. The specific
application of the observer rating will be applied in a prior workshop
conducted by CF.

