## Method

### Design

Figure 1 displays a SPIRIT chart of the
planned study design. The study is a randomized controlled implementation trial
with three parallel treatment arms using a 1:1:1 allocation ratio. A blocked
randomization with blocks of variable length conducted by a random-number
generator (random.org) will be performed. Block length will be determined
randomly (9, 12 or 15 units), before conditions will be randomized within all
blocks separately. An independent research assistant will develop the block list
and conduct the randomization. Patients will be randomized to one of the
following arms: CBT + positive mental imagery induction (PMI), CBT + neutral
mental imagery induction (NMI) and TAU. All arms include an individual CBT
treatment. A cross-therapist design in which any therapist can deliver all three
conditions is applied. Randomization will be focused on patients only, so that
therapists will not see a fixed number of patients per condition. However, we
expect that the block randomization will enable an approximately equal number of
patients in all conditions per therapist. All participants are blind to the
conditions and specific hypotheses. According to the CONSORT statement
concerning the criteria of a pragmatic randomized trial (Zwarenstein et al., 2008) therapists and study coworkers
conducting the information meetings are not blind to allocation. Researchers
involved in data collection and evaluation will be blind to condition labels. An
independent researcher will analyze study data with non-identifying codes of the
conditions. The study includes a longitudinal design with an initial diagnostic
phase (four to five sessions) and the following twelve psychotherapy sessions.
Outcome for the process analysis will be gathered directly after each treatment
sessions. In the intervention analysis, assessments will be made every forth
session: at the start of treatment (pre), after fourth (mid-4), after eighth
(mid-8) and after twelfth treatment session (post-12). In addition, videotapes
of treatment sessions 2, 5 and 8 will be analyzed with an observer rating.

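### Observers who rate uncut tapes of sessions 2, 5 and 8 can tell the arm from the recording, so withholding condition labels does not blind them

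*Protocol article*

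**What the plan says.** All references are to the protocol article.

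- **Who is blind.** Under Design, researchers "involved in data collection and evaluation will be blind to condition labels". Bias Minimization goes further and describes researchers with these tasks as blind to the randomization itself. Observer Rating says only "Independent research assistants will analyze the videotapes" and does not mention masking.
- **When recording starts.** Under Conditions and Experimental Session, "Every session will start with an initial greeting of" "patients and the start of video recording". Standard Procedure at CMHP says that the therapy rooms record both video and audio.
- **What follows in the imagery arms.** "Experimental sessions will be conducted from session one to eight in the active" arms. Each such session opens with a spoken mood rating, about six minutes of audio from a loudspeaker on the table (grey for positive imagery, PMI; black for neutral imagery, NMI), a second mood rating, and about one minute in which the patient tells the therapist what was imagined. Regular therapy starts after that. Treatment as usual (TAU) has no micro-intervention.
- **What is rated.** Under Design, videotapes "of treatment sessions 2, 5 and 8 will be analyzed with an observer rating". Observer Rating gives the resolution, "To assess relevant aspects on a minute-by-minute basis within treatment" sessions, and the content: several aspects of resource activation ("of problems, global resource activation) and PA from video recordings of" the sessions).

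**The concern.** An independent rater is not necessarily a blind one. A rater who hears a positive script, a neutral script or no script knows the arm without seeing a label. The blinding described under Design and Bias Minimization would then not be delivered for the people who turn video into data.

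The ROMA rating is the only entry in Table 1 that is not patient self-report, and the only one with minute-level resolution. Patients take part in the imagery themselves, so an observer who does not know the arm is the natural check on self-reported affect. The article hypothesises higher in-session PA under PMI than in the other arms. A rater who knows the arm, and may know the hypothesis, cannot provide that check free of expectation.

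A second issue arises if the opening minutes are coded. The score then combines what happens while the intervention is being delivered with what happens in the therapy that follows. Those are different questions.

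**Working it through.** No figure in the article bears directly on this point, and the sample size calculation does not involve the observer rating. The check consists of setting the statements side by side, plus two small calculations.

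**1. Do the rated sessions contain the micro-intervention?** Rated sessions: {2, 5, 8} (Design, Table 1). Sessions with micro-intervention: {1, ..., 8} (Conditions and Experimental Session). The overlap is {2, 5, 8}, that is 3 of 3. Sessions 9 to 12, which have no micro-intervention, are not rated.

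**2. Is the micro-intervention on the tape?** Recording starts at the greeting, before the first mood rating, and the rooms record sound. An uncut tape therefore contains the following:

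| Opening of the tape | PMI | NMI | TAU |
|---|---|---|---|
| Spoken mood rating, before and after | yes | yes | not described |
| Audio script, about 6 min | positive | neutral | none |
| Recounting, about 1 min | positive situation | non-emotional situation | none |
| Loudspeaker on the table | grey | black | none described |

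The sound alone separates the three arms. The speaker colour adds to this only if the speaker is in the camera's view, which the article does not say.

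**3. Does this conflict with the blinding statements?** Blinding to labels can hold literally while the arm is plain from the tape. Blinding to the randomization, as in Bias Minimization, cannot hold for a rater of an uncut tape. Neither statement names the video raters. They come under it because coding video is collecting and evaluating data.

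**4. How much of the tape is the opening?** The stated parts are 6 + 1 = 7 minutes; the time for the two mood ratings is not given. Session length L is not given either, so it is assumed to lie between 45 and 60 minutes:

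- L = 45: 7/45 = 15.6%
- L = 50: 7/50 = 14.0%
- L = 60: 7/60 = 11.7%

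This is the share of minutes at stake if the whole tape is coded. It is not an effect size. Turning it into one would need the difference in coded PA between those minutes and the rest, and the article gives nothing from which to derive that.

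**5. How many tapes?** If three tapes are rated for each of up to 120 patients, 120 × 3 = 360 tapes. With 1:1:1 allocation about two thirds, 240, would contain a micro-intervention.

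**The case against.** The strongest reply is that the article does not say which minutes raters receive. It separates the micro-intervention from the regular session that follows, and leaves the application of the rating system to a workshop. Clip selection is the kind of detail that a coding manual holds. This stands in part: a reader might infer that the raters cannot be blind at all, but that is true only of uncut tapes. What remains is that the article states the start of recording, the rated sessions, the coding resolution and who is blind, and these fit together only if the tapes are edited, which it does not mention.

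Three further inferences are tempting and should not be drawn.

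- **That ROMA is the only measure of session affect in all arms.** The PANAS, which asks about the current moment, and the single mood item are both collected after every session in every arm. ROMA is unique only in being observer-rated and minute by minute.
- **That the script inflates PMI by a calculable amount.** For about six minutes the patient listens and imagines. Observers might code more or less PA in that time, and nothing says that the audio itself is coded. Any shift in standard deviations would rest wholly on assumed inputs.
- **That the trial's main results are compromised.** ROMA is listed as neither a primary nor a secondary outcome, and the power calculation does not rest on it.

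It can also be argued that including the opening is legitimate, since raising in-session PA is the intervention's aim. That is fair as a manipulation check. It does not make the rating blind, and it does not answer the question of carry-over.

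**Conclusion.** The point holds for tapes rated as recorded. All three rated sessions open with the micro-intervention in both imagery arms, so sound alone reveals the arm, and withholding labels does not deliver the blinding stated under Design and Bias Minimization. If the opening is coded, about 12 to 16% of minutes mix delivery with carry-over, in a direction and to an extent that the documents do not allow one to state.

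This rests on two plain readings, neither of them explicit: that raters see the tape from its start, and that video raters count among the researchers said to be blind. The percentage also rests on the assumed session length of 45 to 60 minutes.

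Severity is moderate. The observer-rated PA and resource activation are affected. The named primary and secondary outcomes, all self-report, are not.

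**What to change.** Before any coding starts:

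1. Give raters clips that begin after the recounting minute. Start TAU clips at a matched session minute, so that a visible greeting or a longer tape does not mark that arm.
2. If the loudspeaker is visible, crop or mask it in the video. Moving it during the session would alter the described procedure and is not needed for this purpose.
3. Code the opening block, if at all, separately, and report it as an unblinded manipulation check.
4. Have raters record a guess of the arm after each clip, and report the guesses by arm.
5. Align Design, Observer Rating and Bias Minimization on who is blind and to what. The same edit should settle the therapists, whom Design describes as not blind to allocation and Bias Minimization as blind.

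The cost is trimming up to 360 recordings, masking where needed, and a short addition to the coding instructions. The opening minutes leave the blinded score, and later talk in a session may still occasionally reveal the arm; the recorded guesses would show how often. Timing matters, because a rater who has watched the opening of a tape cannot be made blind to it afterwards.
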